**Study size**

This is a pilot study and thus no formal study size calculation was undertaken since no estimate of effect size is available and the study is to be used to determine this as well as the feasibility of the planned multicentre study.

We plan to recruit 150 patients in each of the 2 trial arms. This would enable in the full sample detection of a small to medium effect size (0.4 SD of the main outcomes (Rankin, Nottingham EADL and EuroQuol) with 90% power and with a 5% two sided significance level. The study size was determined considering the following factors:

Ronning et al included almost 600 patients in their study of routine oxygen supplementation and did not find an overall difference on functional outcome at one year. There was a trend towards a better result with oxygen treatment in the 240 subjects with severe stroke, although this finding was not backed up by the use of a suitable test for heterogeneity. Our protocol may be more likely to show benefits because oxygen is given for longer, and titrated according to baseline oxygen saturation.[[46]](#endnote-47) However, given the data of the above study it is likely that any observed effect is small. This pilot study will provide us with data to inform a study size calculation.

Over the last year we performed a small study of the effects of oxygen supplementation for 24 hours within 3 days of admission on oxygen saturation. It showed a significant improvement of oxygen saturation in the treated group, but the study was not powered to look at functional outcomes. It took 6 months to recruit 50 patients for this study.[[47]](#endnote-48) It is therefore likely that we will be able to recruit 300 patients over three years.

**Statistical Advice**

The statistical aspects of study design and analysis have been discussed with [name] and [name] who both have wide experience in statistics of medical trials and trial design, and who are co-applicants. Because we have no data on the expected effect size form other trials or on the SD of the main outcome (death and disability) in our patient population we are not yet in a position to do a study size calculation.

[name]

Department of Mathematics

Keele University

[[contact]](mailto:[contact])

**Data Analysis**

Data entry and analysis will be performed by members of the study team ([name], [name], [name]) with advice from [name].

**STUDY TIMETABLE**

July 2004 start of recruitment

July 2005 100 patients recruited

July 2006 200 patients recruited

July 2007 recruitment complete

Jan 2008 follow-up complete

April 2008 statistical analysis complete

October 2008 research paper submitted for publication

**Stroke Oxygen Study**

**Randomisation Form**

Name of person completing this form Centre number

STEP 1 ELIGIBILITY FOR TRIAL INCLUSION

| Admitted with acute stroke within the preceding 24 hours | YES | NO |
| --- | --- | --- |
| Not expected to die within a few months from a non-stroke related illness | YES | NO |
| No definite indication for continuous oxygen treatment | YES | NO |
| No definite contraindication to continuous oxygen treatment | YES | NO |

Please proceed to patient details if all answers to Q1 are YES

**STEP 2 PATIENT DETAILS**

Name Sex Date of birth

Date and time of stroke onset (24 h clock)

Side of hemiparesis

| Right | Left | Neither | Both Sides |
| --- | --- | --- | --- |

Glasgow Coma Scale (please circle one response in each row)

| Eye  Opening | None (1) | To pain  (2) | To speech  (3) | Spontaneous (4) |  |  |
| --- | --- | --- | --- | --- | --- | --- |
| Motor Response | None (1) | Extension  (2) | Abnormal  flexion (3) | Withdrawal (4) | Localizes  to pain (5) | Obeys  commands (6) |
| Verbal response | None (1) | Incomprehensible (2) | Inappropriate (3) | Confused (4) | Oriented  (5) |  |

**STEP 3 PROGNOSTIC FACTORS (please circle the yes or no and complete oxygen saturation)**

| 1. Living alone before the stroke | YES | NO |
| --- | --- | --- |
| 2. Independent in Activities of daily living before the stroke | YES | NO |
| 3. Normal verbal response to questions | YES | NO |
| 4. Able to lift the affected arm against gravity | YES | NO |
| 5. Able to walk unaided | YES | NO |
| 6. Oxygen saturation at randomisation | % | |

STEP 4 CONSENT

| 1. Fully informed consent  Before randomisation either 1  or 2 and 3 must be answered as **YES** | YES | NO |
| --- | --- | --- |
| 2. Patient does not disagree with trial | YES | NO |
| 3. Assent from next of kin | YES | NO |

**STEP 5 RANDOMISATION** Please phone (xxxxx) xxxxxxxx for 24 hour randomisation or any queries

Date and time of randomisation (24 h clock)

Randomisation number

Treatment allocated (circle the treatment the patient was randomised to receive)

| No routine oxygen | 2l/min continuously for 72 hours | 3l/min continuously for 72 hours |
| --- | --- | --- |
|  | 2l/min for 3 nights | 3l/min for 3 nights |

Treatment start time (24 h clock) PTO for Baseline Neurological Assessment

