# STUDY DESIGN

A randomised controlled open pilot study of routine fixed dose oxygen supplementation versus no routine oxygen treatment.

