**DETAILED PLAN OF INVESTIGATION**

**Summary of the study**

This is a study of the effect of routine oxygen supplementation early after acute stroke. A brief synopsis of the trial structure is given in the attached Flow Chart. Subjects will be randomised to receive fixed dose oxygen or no routine oxygen for 72 hours. Oxygen saturation will be recorded over night by pulse oximetry on night 2. The patient will be assessed by a member of the research team on day 3 and week 1 after trial enrolment. At 3 months the researcher will consult the hospital computer system and the patient's notes to find out whether the patient was discharged from hospital and to where. At 6 months after trial enrolment the patient will be sent a questionnaire with questions relating to their daily functional abilities.

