**Intervention**

Patients will be randomised to one of two treatment groups:

1. Treatment group 1: no routine oxygen supplementation during the first 3 days of randomisation.
2. Treatment group 2: oxygen per nasal cannula continuously (day and night) at a flow rate of 3l/min if baseline oxygen saturation is 93% or at a rate of 2l/min (if baseline oxygen saturation 93%) with humidification during the first 3 days after randomisation. Patients who develop definite indications or contraindications for oxygen treatment during the trial will be treated according to clinical need, irrespective of study treatment allocation.

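### Step 5 of the Randomisation Form offers two nights-only oxygen allocations that the two-arm, continuous 72-hour design does not contain

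*Protocol*

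**What the plan says.** The protocol sets out a two-arm comparison. Study Design calls the trial "A randomised controlled open pilot study of routine fixed dose oxygen supplementation versus no routine oxygen treatment". The Summary of the study gives the duration: "Subjects will be randomised to receive fixed dose oxygen or no routine oxygen for 72 hours". Under Intervention, the active group receives "oxygen per nasal cannula continuously (day and night") at one of two flow rates, chosen by baseline saturation, for the first three days. Study size counts the arms: "We plan to recruit 150 patients in each of the 2 trial arms".

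Step 1 of the Randomisation Form uses the same idea of treatment. One of its eligibility items reads "No definite indication for continuous oxygen treatment".

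Step 5 of that form departs from this. The instruction is to "circle the treatment the patient was randomised to receive". The cells below it show control, the two continuous 72-hour regimens (2 and 3 l/min) and, in a separate row, "2l/min for 3 nights" and "3l/min for 3 nights".

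**The concern.** The field is headed as the randomised allocation, so each cell in it should be a treatment to which a patient can be randomised. Two cells are not. Read literally, the form implies a third, nocturnal arm at two flow rates.

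The form is a working document. Under Randomisation and initial assessment and under Research Staff, the protocol allows admissions and emergency staff outside the core team to complete it at any hour. Two things could go wrong:

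- **Misrecording.** The wrong cell is marked but the patient receives continuous oxygen as intended.
- **Misdelivery.** The marked cell is followed and oxygen is given only at night.

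The second matters more. It would be unclear whether that patient was treated as allocated. Main outcomes lists protocol violations as a feasibility measure, and Statistical analysis plans an analysis without violators. Both need to know what was allocated and what was delivered.

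**Working it through.** The check compares texts; the plan states no figure to reproduce.

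**1. Count the allocations.**

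| Allocation | Intervention section | Form, Step 5 |
| --- | --- | --- |
| Control, no routine oxygen | defined | printed |
| Continuous, 2 l/min, 72 hours | defined | printed |
| Continuous, 3 l/min, 72 hours | defined | printed |
| Nights only, 2 l/min | not defined | printed |
| Nights only, 3 l/min | not defined | printed |

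Printed: 1 + 2 + 2 = 5. Defined: 1 + 2 = 3. Undefined: 5 − 3 = 2. This counts form entries; it does not measure risk.

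**2. Could the nights-only cells be another wording for 72 hours?** No. The continuous regimens have their own cells in the same field, and the Intervention section specifies day and night. The protocol does not define a night for treatment. If one borrows the 21:00 to 9:00 oximetry window on the Day 3 form (12 hours), three nights give 3 × 12 = 36 hours, which is 36/72 = 50% of the intended exposure. That is an illustration under an assumption, but it shows that the regimens differ.

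**3. Does another part of the protocol explain the row?** Randomisation and initial assessment says that the minimisation criteria were put on the form with the later multicentre trial in mind. Those are the prognostic items in Step 3, and nothing is said about nocturnal treatment. The recall question on the last page of the 6-month questionnaire offers three days of oxygen, oxygen only when needed, or not known; it has no nights-only choice. The flow chart mentioned in the Summary is not in the text at hand. A nocturnal arm there would itself conflict with Intervention and Study size.

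**4. What happens if a nights-only cell is marked?**

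- *Group membership:* unaffected, since both cells are oxygen cells.
- *Intended flow rate:* recoverable. Step 3 of the same form records saturation at randomisation, and the background section on oxygen supplementation assigns 2 l/min above 93% and 3 l/min otherwise.
- *Intention-to-treat comparison:* unaffected, because patients are analysed in the group allocated.
- *Regimen delivered:* not reliably recoverable. Oximetry runs overnight, when a nights-only patient would be on oxygen. The Day 3 compliance item is a single observation. Its middle category covers patients without oxygen in place who are reported to be receiving it, and a nights-only patient seen by day could fall there.

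**The case against.** The strongest reply is that the row is leftover text with almost no consequence. Step 5 records an allocation given by telephone; it does not generate one. A nights-only cell would be marked only by a slip, or if the telephone service announced a regimen that the protocol lacks. Recruiters are to be trained or informed, and Research Staff expects the research team to randomise most patients. The form also looks unfinished: its telephone number is a placeholder, and it asks for a centre number in a single-centre pilot. The fault lies in the form and not in the design.

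All of that stands, and it is why the point is minor.

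A second reply is that delivery is recorded elsewhere: compliance on the Day 3 form, and oxygen prescribed outside the protocol on the week 1 form. This stands in part. A recording slip alone leaves delivery untouched. The main objectives describe violation as oxygen given outside the protocol, and the week 1 item captures that without reference to Step 5. However, that item asks about continuous oxygen given for clinical reasons. It would not pick up an oxygen-group patient who received less than allocated, and the Day 3 item cannot be relied on to do so. The remaining risk is therefore confined to patients actually treated at night only, and it bears on the violation outcome and the analysis excluding violators.

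**Conclusion.** The concern holds. Step 5 contradicts the Intervention section and every other statement of the design, and the protocol as shown gives no explanation. It is an inconsistency in an operational form; the design itself is coherent.

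Severity is minor. Two of five printed allocations are undefined. The intention-to-treat comparison and the sample size are not affected. The possible harm is an occasional misrecorded or misdelivered regimen. The documents give no rate at which a nights-only cell would be marked or followed, so no number of patients and no loss of power can be stated.

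The conclusion rests on the two-arm, continuous regimen being the intended one, which all the descriptive sections support. It also rests on the missing flow chart not defining a further arm.

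**What to change.** Delete the nights-only row from Step 5. The field then lists three choices: control; continuous oxygen at 2 l/min for 72 hours; continuous oxygen at 3 l/min for 72 hours. Printed and defined allocations then agree, three against three.

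If forms have already been used, check any with a nights-only cell marked against the telephone randomisation record for that randomisation number. Establish what was delivered, and classify the patient for the violation count and the analysis excluding violators on that basis.

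The cost is one table row and one reprinted form, with no change to sample size or trial conduct.

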**Stroke Oxygen Study**

**Baseline Neurological Assessment (Admission)**

Name Randomisation no

**Scandinavian Stroke Scale**

**(tick one box in each group, for items marked with* score the affected side)**

**Consciousness:**

- **6** fully conscious
- **4** somnolent,

can be awaked to full consciousness

- **2** reacts to verbal command,

but is not fully conscious

**Orientation:**

- **6** correct for time, place and person
- **4** two of these
- **2** one of these
- **0** completely disorientated

**Speech:**

- **10** no aphasia
- **6** limited vocabulary or incoherent speech
- **3** more than yes/no, but not longer sentences
- **0** only yes/no or less

**Facial palsy:**

- **2** none/dubious
- **0** present

**Eye movement:**

- **4** no gaze palsy
- **2** gaze palsy present
- **0** conjugate eye deviation

**Total Score**

**Arm, motor power *:**

- **6** raises arm with normal strength
- **5** raises arm with reduced strength
- **4** raises arm with flexion in elbow
- **2** can move, but not against gravity
- **0** paralysis

**Hand, motor power *:**

- **6** normal strength
- **4** reduced strength in full range
- **2** some movement, fingertips do not reach palm
- **0** paralysis

**Leg, motor power *:**

- **6** normal strength
- **4** raises straight leg with reduced strength
- **5** raises leg with flexion of knee
- **2** an move, but not against gravity
- **0** paralysis

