**Consent**

Fully informed consent will be sought from all competent subjects. In subjects who are conscious, but not fully competent to comprehend the information given and make a reasoned decision we will provide a simple explanation of the trial and seek the patient's agreement, but also seek assent from the next of kin. In subjects unable to participate in the decision process in any way we will seek assent of the next of kin only. If an incompetent subject has been included in the trial without giving fully informed consent we will strive to obtain fully informed consent as soon as the patient is able to do so. Consent will be sought by the doctor randomising the patient or by a member of the research team. All doctors randomising patients into the study will be given appropriate information about the trial treatment, potential effects and side effects and the assessment protocol by a member of the research team.

*The reason for including patients who are unable to give fully informed consent*

It is crucially important to include as wide a spectrum of stroke subjects as possible, and, in particular, patients with severe strokes. Patients with severe strokes may be more likely to develop hypoxia, and a recent study has suggested that patients with severe strokes may be more likely to benefit from oxygen than patients with mild strokes. However, patients with severe strokes are more likely to be confused, drowsy or dysphasic and thus unable to give informed consent. Exclusion of subjects unable to give informed consent is thus likely to bias trial outcome.

*The reason for involving the doctor admitting the patient in gaining consent for the study*

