**Main outcomes**

Comparisons will be made between the treatment and control group to determine:

1. Effect size:

- Death and disability (Rankin >3) at 6 months
- Scandinavian Stroke Scale week 1
- Mortality up to 6 months
- Rankin Score at 6 months
- Nottingham EADL score at 6 months

2. Potential Side effects of the study treatment

- Rate of infections (pyrexia or antibiotic treatment at week 1)
- Agitation (sedative or antipsychotic medication at week 1)
- Physiological indicators of stress (tachycardia, hypertension)

3. To assess the feasibility of the study protocol we will examine

- Protocol violations
- Recruitment rate
- The relation between the number of recruited and excluded patients
- The percentage of completed 6-month questionnaires

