**Leg, motor power *:**

- **6** normal strength
- **4** raises straight leg with reduced strength
- **5** raises leg with flexion of knee
- **2** an move, but not against gravity
- **0** paralysis

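### The Scandinavian Stroke Scale leg item has its 4- and 5-point levels in reverse order on both the baseline and week-1 forms

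*Protocol*

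**What the plan says.** The Protocol prints the Scandinavian Stroke Scale twice: in the Baseline Neurological Assessment, and in Week 1, Assessment form 2b. The two versions are the same. The assessor is told to "tick one box in each group", and each form has a field for the total.

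- **Leg, motor power** (both forms): the points read 6, 4, 5, 2, 0 from top to bottom. The second line, "raises straight leg with reduced strength", carries 4. The third line, "raises leg with flexion of knee", carries 5.
- **Arm, motor power** (both forms): the points read 6, 5, 4, 2, 0. The second line, "raises arm with reduced strength", carries 5. The third line, "raises arm with flexion in elbow", carries 4.
- **Consciousness** (both forms): only 6, 4 and 2 are offered. The lowest level is for a patient who "reacts to verbal command" without being fully conscious.

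Under *Main outcomes*, the first group (effect size) includes "Scandinavian Stroke Scale week 1". On who may enter, the *Consent* section states: "In subjects unable to participate in the decision process in any way we will seek assent of the next of kin only".

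**The concern.** On this scale a higher score means a better neurological state. In the leg item the descriptions run from best to worst, but the second and third point values do not follow them. A patient who can lift a straight leg weakly is scored below one who can lift it only by bending the knee. The same pattern on both forms suggests a copying slip carried from one to the other.

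What is at stake is the week-1 total as a between-group comparison, and the reuse of the forms. The pilot is meant to inform a larger multicentre trial, so an uncorrected form could be carried into it.

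The consciousness item raises a related question. A patient who gives no response to speech fits none of its three boxes, yet one box per item is required. The form does not say how that patient is to be scored.

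**Working it through.** **1. Order and range of every item, as printed (the same on both forms)**

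| Item | Points, top to bottom | Descending? | Has a 0 level? |
|---|---|---|---|
| Consciousness | 6, 4, 2 | yes | **no** |
| Orientation | 6, 4, 2, 0 | yes | yes |
| Speech | 10, 6, 3, 0 | yes | yes |
| Facial palsy | 2, 0 | yes | yes |
| Eye movement | 4, 2, 0 | yes | yes |
| Arm | 6, 5, 4, 2, 0 | yes | yes |
| Hand | 6, 4, 2, 0 | yes | yes |
| Leg | 6, 4, 5, 2, 0 | **no** | yes |
| Gait | 12, 9, 6, 3, 0 | yes | yes |

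Maximum total = 6 + 6 + 10 + 2 + 4 + 6 + 6 + 6 + 12 = 58. Minimum with every item ticked = 2, because consciousness stops at 2. Leg is the only item out of order, and consciousness is the only item without a 0.

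**2. Error in one patient's total**

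Take the arm item's order as the intended one.

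- Weak straight-leg raise: printed 4, intended 5, error 4 − 5 = −1.
- Knee-flexion raise: printed 5, intended 4, error 5 − 4 = +1.
- Any other leg level: error 0.

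The error is therefore 1 point of 58 for patients at these two levels and nil for everyone else. The maximum of 58 is unchanged.

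**3. Error in a group mean**

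Let *a* be the share of a group at the straight-leg level and *b* the share at the knee-flexion level. The mean error is *b* − *a*. The Protocol gives neither share. Assuming each lies between 0 and 30%:

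- *a* = 0.30, *b* = 0 gives −0.3 points.
- *a* = 0, *b* = 0.30 gives +0.3 points.
- *a* = *b* gives 0.

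**4. Error in the difference between groups**

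The scoring rule is the same in both groups, so the error in the difference is (*b* − *a*) in the oxygen group minus (*b* − *a*) in the control group. It is zero when *b* − *a* is equal in the two groups. If treatment moved a share *m* of patients from knee flexion to straight-leg raise by week 1, the true contribution to the difference would be +*m* and the recorded one −*m*, an error of 2*m*:

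| *m* (assumed) | True | Recorded | Size of error |
|---|---|---|---|
| 0.05 | +0.05 | −0.05 | 0.10 |
| 0.10 | +0.10 | −0.10 | 0.20 |
| 0.20 | +0.20 | −0.20 | 0.40 |

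The sign of this one component is reversed, but it stays under half a point on a 58-point scale over the assumed range.

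**5. What is not touched**

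The six-month outcomes do not use this scale. The detectable-difference statement under *Study size* refers to Rankin, Nottingham EADL and EuroQuol, so it does not depend on it either.

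**6. Consciousness**

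The *Consent* section admits patients who can take no part in the decision and stresses severe strokes. The Glasgow Coma Scale on the Randomisation Form includes levels for no response and for response to pain only. The eligibility section does not exclude coma. An unresponsive patient could therefore enter and would fit no box in this item. Whether the cited scale has a lower level is not stated in the Protocol.

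**The case against.** The strongest reply is that the slip is small, common to both groups and recoverable. It affects two of five levels of one item by 1 point each, in opposite directions. Assessors tick worded boxes, so completed forms can be rescored. The week-1 score is one of five effect-size items, and the *Month 6 assessment* section reserves the main outcome for death and disability at six months. All of this stands and limits the weight of the point. It does not remove the inconsistency, because the order is wrong on the face of both forms.

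Three stronger readings are tempting, and the Protocol does not support them.

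- *A patient improving from knee flexion to straight-leg raise is recorded as worse, so an outcome has the wrong sign.* The arithmetic is right for a change score: −1 instead of +1. However, the outcome listed is the week-1 score itself, and no change from baseline on this scale is named. The *Week 1 assessment* section does mention neurological deterioration, but it does not define it by this scale.
- *The baseline score is the trial's main severity measure.* The section on randomisation and initial assessment lists it beside the Glasgow Coma Scale and the prognostic factors. The factors considered for later minimisation do not include it.
- *The missing 0 for consciousness is an error that inflates scores or leaves totals missing in the sickest patients.* If the cited scale stops at 2, the form is faithful to it. The *Consent* section describes severe-stroke patients as confused, drowsy or dysphasic, which is not the same as unresponsive. The Protocol also does not say that an unticked item makes the total missing; summing the ticked points would simply add nothing for it.

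**Conclusion.** The point holds for the leg item. The 4- and 5-point levels are in reverse order on both forms, shown by the broken descending sequence and by the arm item. Each affected total is off by 1 point of 58, and the two levels are misranked in the week-1 score. With assumed shares of 0 to 30% at each level, a group mean moves by at most 0.3 points either way. The between-group difference is affected only if *b* − *a* differs between the groups.

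The conclusion assumes that the arm item shows the intended order. That is strong internal evidence, but it should be confirmed against the cited scale. The number of patients affected is unknown.

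The consciousness item is a gap to check: unresponsive patients are not excluded and have no box, but the documents cannot show that the form departs from its source. Overall this is a minor correction. It does not affect the six-month outcomes or the study size.

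**What to change.** 1. Check the leg item against the cited scale. If it agrees with the arm item's order, print 5 for the weak straight-leg raise and 4 for the knee-flexion raise on both the baseline form and form 2b.
2. Rescore any completed form from the ticked wording and not from the printed number: add 1 to the total where the straight-leg level was ticked, and subtract 1 where the knee-flexion level was ticked. Enter item-level ticks as well as totals, so that the rule can be applied and audited.
3. Check the consciousness item against the same source. If the source has a lower level, restore it on both forms. If not, state in writing how a patient who does not respond to a spoken command is scored.

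The cost is two reprinted forms, one recode rule and one scoring note. No new data and no extra visit are needed.
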